### Participant timeline {13}

See Table 1 for the participant timeline.

#### Clinical parameters collected at inclusion by the investigator

Data relating to admission: age, sex, severity score quantified by the Simplified Acute Physiologie Score II (SAPS II), comorbidities, including pre-existing respiratory or cardiac pathology, condition that precipitated the acute respiratory failure responsible for the initiation of ventilatory assistance.Physiological values: temperature, blood pressure, respiratory rate, VAS-dyspnea, VAS-anxiety.Oxygenation modalities: standard oxygen (flow rate), HFNCO (high-flow nasal cannula oxygenation) (flow rate and inspired fraction of oxygen) or non-invasive ventilation (inspired fraction of oxygen, level of inspiratory assistance, level of positive expiratory pressure); Arterial blood gases: PaO_2_, PaCO_2_, pH, HCO3−, SaO_2_.Associated analgesic, anxiolytic or psychotropic treatments administered during the first 24 h.

#### Clinical data collected every 4 h

Dyspnea-VAS (for 24h), Anxiety-VAS (for 24h), Pain-VAS (for 24h), CAM-ICU (for 48h), Glasgow Coma Scale (GCS) (for 48h), respiratory rate (for 24h), change of oxygenation technique (for 48h).

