### Eligibility criteria {10}

Inclusion criteria are the followings:Adult patients ≤ 75 years,Admitted in intensive care for an acute respiratory failure defined as a respiratory rate> 24/min or signs of respiratory distress such as labored breathing or paradoxical inspiration, or SpO2 <90% in ambient air,Spontaneous ventilation, either under standard oxygen, high flow oxygen, or non-invasive ventilation,Dyspnea ≥40 mm on a Dyspnea-VAS from zero (no dyspnea) to 100 mm (worst possible dyspnea),Richmond agitation and sedation scale (RASS) between 0 and 2,No confusion, as defined by the Confusion Assessment Method for ICU (CAM-ICU), andSigned informed consent of the patient, a relative, or emergency consent process.

Non-inclusion criteria are the followings:Intubated patient or intubation planned upon admission,Unable to respond to a visual analog scale (hearing or visual impairment, insufficient command of French, previous psychiatric or cognitive disorders known),Moribund patient,Contraindication to opioids (known hypersensitivity to opioids, severe renal insufficiency (creatinine clearance <30 ml/min), severe hepatocellular insufficiency (factor V <50%)Any formal contra-indication of opiates,Opioid use within the 24 h before inclusion,Pregnancy or breastfeeding,Minor and protected adult,Exclusion period due to inclusion in another clinical trial,Previous inclusion in this study, andNo affiliation to social security.

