### Sample size {14}

This is a pilot study. There is very limited data on the intensity of dyspnea in non-intubated patients admitted to the ICU for an acute respiratory failure [3, 6]. Based on these studies, we estimated that mean Dyspnea-VAS over the first 24 h, our primary outcome would be 37 mm in the control arm. We hypothesized that the reduction of mean Dyspnea-VAS over the first 24 h (primary outcome) would be 25 mm, which is 2.5 times the currently admitted minimal clinically important difference (MCID) [27], with a standard deviation of 26 mm. In the experimental arm, mean Dyspnea-VAS over the first 24 h would subsequently be 12 mm. Therefore, with a power of 80%, a one-sided alpha risk of 10% (in order to provide a signal of efficacy without missing a difference), and considering that a non-parametric test will be used, we calculated that 22 patients should be recruited (11 per group).

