## Assignment of intervention: allocation

### Sequence generation {16a}

The randomization list will be prepared by the clinical trial research unit of the hospital. Randomization ratio will be 1:1. The randomization list will be computer-generated with random permuted blocks. Randomization will be performed after inclusion of the patient on the electronic case report form (eCRF) (Cleanweb, Télémédecine Technologies, Boulogne-Billancourt, France).

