#### Secondary outcomes

Quantitative variables will be compared between the two arms with a Mann-Whitney test. Categorical variables will be compared between the two arms with a chi-square test or a Fisher’s exact test as appropriate.

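### The 24 h oxygenation-technique outcome has no direction, so moving to less support and moving to more support count as the same event

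*Protocol article*

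**What the plan says.** All references are to the protocol article.

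- **Outcomes {12}, Secondary outcome measures.** One outcome is the proportion of patients requiring a move between oxygenation techniques in the first 24 h. The techniques are not ordered, and a move up is not separated from a move down.
- **Participant timeline {13}, Clinical data collected every 4 h.** The matching item is "change of oxygenation technique (for 48h", again without direction.
- **Eligibility criteria {10}.** Patients enter with "Spontaneous ventilation, either under standard oxygen, high flow oxygen, or non-invasive ventilation".
- **Statistical methods {20a}, Secondary outcomes.** "Categorical variables will be compared between the two arms with a chi-square test or a Fisher’s exact test as appropriate".
- **Methods for additional analyses {20b}.** None are planned.
- **Data available for direction.** The technique in use is recorded at inclusion (Clinical parameters collected at inclusion). Table 1 schedules respiratory support at inclusion, every 4 h to day 1, at 24 h and at 48 h.

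**The concern.** Three starting techniques make moves in both directions possible from the first hour. A patient taken off NIV onto standard oxygen because of improvement and a patient put on NIV because standard oxygen was failing each satisfy the event as written. A single proportion then adds good and bad courses together. A higher proportion under morphine could mean faster weaning or respiratory worsening, and equal proportions could hide opposite courses.

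The background section names respiratory depression as the main historical obstacle to morphine for dyspnea. A change in respiratory support short of intubation is a natural place to look for it, and no listed outcome is defined as escalation short of intubation.

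The any-change rate also depends on where patients start. Under any ordering, a patient on the lowest technique can only move up, and one on the highest can only move down or be intubated. With 11 patients per arm, a chance imbalance in starting technique can shift the proportion without any treatment effect.

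**Working it through.** **The plan's own figure.** The article gives no figure for this outcome. Its only sample-size figure concerns the primary outcome, and it reproduces:

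- Inputs (Sample size {14}): difference 25 mm, SD 26 mm, one-sided alpha 10%, power 80%, non-parametric test.
- n per arm = 2 × [26 × (1.2816 + 0.8416) / 25]² = 9.75.
- Allowing for the Mann-Whitney efficiency of 3/π: 9.75 × π/3 = 10.2, rounded up to 11 per arm, 22 in total.
- Simulated power of the one-sided Mann-Whitney test at 11 per arm (normal data, means 37 and 12 mm, SD 26 mm, 20,000 runs): 80.2%.

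So 11 per arm stands, and it is the denominator used below.

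**What the event includes.** With three permitted starting techniques and no ordering, the definition covers every move from any technique to any other. Nothing in the outcome, the collection item or the test separates the directions.

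**Illustration of masking.** The counts are assumptions, because the documents give no transition rates. P values are from Fisher's exact test, taken as two-sided; the article does not state sidedness for secondary outcomes.

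| Assumed course | Morphine: escalated / weaned | Placebo: escalated / weaned | Any change | p | Escalation only | p |
|---|---|---|---|---|---|---|
| Extreme | 0 / 5 | 5 / 0 | 5/11 vs 5/11 | 1.00 | 0/11 vs 5/11 | 0.035 |
| Milder | 1 / 4 | 4 / 1 | 5/11 vs 5/11 | 1.00 | 1/11 vs 4/11 | 0.31 |

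Arithmetic for the escalation columns, with 5 escalations among 22 patients and C(22,5) = 26,334:

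- Extreme: C(11,0) × C(11,5) / 26,334 = 462 / 26,334 = 0.0175; doubled, because the distribution is symmetric, 0.035.
- Milder: add C(11,1) × C(11,4) / 26,334 = 11 × 330 / 26,334 = 0.138, giving 0.155; doubled, 0.31.

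**The converse.** An any-change result of 5/11 on morphine against 0/11 on placebo is the same kind of table, p = 0.035. It is that value whether the five morphine patients were all weaned or all escalated. A small p value therefore says no more about benefit or harm than a large one.

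**The case against.** Five points can be made on the other side.

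1. *This is derivation detail for the full protocol or the statistical analysis plan, neither of which is shown.* Coding rules often do sit there. But the article states the event itself, and that event pools both directions. Splitting it produces different outcomes, not a finer derivation of the same one.
2. *The outcome speaks of patients requiring the move, which suggests clinical need rather than weaning.* The word leans that way but does not settle the matter: the object is a move between any two techniques, and nothing excludes a step down.
3. *Other outcomes carry the respiratory signal.* Intubation to 48 h, respiratory rate, the time spent on each technique and the adverse events of particular interest do give some direction, which limits the damage. None of them identifies which patients moved up from their starting technique without being intubated.
4. *The extreme example is invented, and in the milder one the directional comparison gives p = 0.31.* Correct. At 11 per arm a directional outcome will often be inconclusive as a test. The gain is that its counts can be interpreted.
5. *Any ordering of techniques comes from outside the article.* Also correct. It is for the investigators to set.

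Two stronger readings are tempting and are not supported. A reader might infer that the outcome window of 24 h contradicts collection to 48 h. Collecting an item for longer than it is analysed is not an error, and 24 h matches the treatment period. A reader might also infer, since NIV sessions are counted, that every patient on intermittent NIV is automatically an event. The documents do not say so; sessions are a separate outcome, and the text simply does not say how planned alternation is to be coded.

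**Conclusion.** The point holds as a defect in the definition of one secondary outcome: as worded, it pools moves to more and to less support, so its result cannot be read as benefit or harm.

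The size is modest. It concerns one of many secondary outcomes in a 22-patient pilot, and the primary outcome and sample size are untouched. The tabulated counts show only that complete masking is possible; how likely it is cannot be judged from the documents. The conclusion rests on reading the outcome literally, and on there being no directional definition in documents that are not shown. It is worth correcting because the correction is nearly free.

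**What to change.** Before unblinding, replace the single proportion with two, both over 24 h and both relative to the technique recorded at inclusion:

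- the proportion of patients with at least one escalation;
- the proportion of patients with at least one de-escalation.

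A patient may count in both. The ordering of techniques should be set in advance by the investigators. State that planned alternation between NIV sessions is not a transition, and whether an intubation within 24 h counts as an escalation, given that intubation is already an outcome of its own. A 48 h result may be added, since the item is collected to that point.

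The cost is one derived variable, a reworded outcome and a slightly longer list of secondary results. No new data should be needed, provided the case report form records which technique is in use at each scheduled step, as Table 1 suggests; this should be confirmed.

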#### Data collected once at 24 h

Intubation, duration of sleep on the first night, quality of sleep on the first night, severity of dry eye, severity of nasal dryness, severity of feeling of gastric distension, constipation, nausea, nurses' adherence to the protocol, nurses’ satisfaction with the protocol, number of NIV sessions, total duration of NIV, NIV tolerance, duration of high-flow oxygen therapy, tolerance of high-flow oxygen therapy, standard oxygen therapy duration, tolerance of standard oxygen therapy, concomitant treatments

#### Clinical data collected once at 48 h

Necessity of intubation, onset of delirium, constipation, nausea.

### Sample size {14}

This is a pilot study. There is very limited data on the intensity of dyspnea in non-intubated patients admitted to the ICU for an acute respiratory failure [3, 6]. Based on these studies, we estimated that mean Dyspnea-VAS over the first 24 h, our primary outcome would be 37 mm in the control arm. We hypothesized that the reduction of mean Dyspnea-VAS over the first 24 h (primary outcome) would be 25 mm, which is 2.5 times the currently admitted minimal clinically important difference (MCID) [27], with a standard deviation of 26 mm. In the experimental arm, mean Dyspnea-VAS over the first 24 h would subsequently be 12 mm. Therefore, with a power of 80%, a one-sided alpha risk of 10% (in order to provide a signal of efficacy without missing a difference), and considering that a non-parametric test will be used, we calculated that 22 patients should be recruited (11 per group).

### Recruitment {15}

The medical ICU of la Pitié-Salpêtrière hospital in which the study is conducted admits annually 1200 patients. Three hundred are admitted for an acute respiratory failure; among them, 150 are not intubated or close to be so on admission. Given the profile of patients admitted in the ICU during the five previous years, we estimated that among these 150 non-intubated patients admitted for acute respiratory failure, 50 will fulfill all the inclusion criteria, among which 35 will fulfill at least one exclusion criteria. Subsequently, we anticipate to include 15 patients per year.

## Assignment of intervention: allocation

### Sequence generation {16a}

The randomization list will be prepared by the clinical trial research unit of the hospital. Randomization ratio will be 1:1. The randomization list will be computer-generated with random permuted blocks. Randomization will be performed after inclusion of the patient on the electronic case report form (eCRF) (Cleanweb, Télémédecine Technologies, Boulogne-Billancourt, France).

### Concealment mechanism {16b}

The administration of the treatment will be done according to the randomization arm following the pre-established randomization list.

Sequentially numbered containers of identical appearance prepared by the pharmacy and containing morphine or placebo will be stored in the ICU. The container with the smallest number available in the department's stock should be assigned to the newly included patient in order to proceed with the randomization.

### Implementation {16c}

After randomization by attribution of the container with the smallest number to the newly included patient, the investigator will report the container number in the eCRF.

## Assignment of interventions: blinding

### Who will be blinded {17a}

Trial participants, researchers involved in the study, and outcome assessors will be blinded. A research nurse who is not involved in the management of patients will be in charge of preparing the treatments from the container. The treatment will be administered by a nurse blinded to the treatment received.

### Procedure for unblinding if needed {17b}

Unblinding will be permissible in case of severe adverse effects.

## Data collection and management

### Plans for assessment and collection of outcomes {18a}

Data will be collected from electronic patient records or by asking the patient and collected with a case report form. Once patients are enrolled, baseline data will be collected. To guarantee consistent assessment, researchers are uniformly trained. The investigator and the study coordinator will be responsible for data collection.

### Plans to promote participant retention and complete follow-up {18b}

No participants will be lost to follow-up as the patients will remain in the ICU until the end of the study.

### Data management {19}

The designated staff will enter the data into the eCRF (Cleanweb, Telemedicine Technologies, Boulogne-Billancourt, France) under the supervision of the principal investigator who is responsible for ensuring that data collected are complete, accurate, and that entry is performed in a timely manner. A data manager will be in charge of checking missing or inconsistent data providing queries to be solved. In case of missing data, the reason will be noted. Corrections, with the reason for the corrections, will also be recorded/tracked in the eCRF.

After resolution of all queries, the database will be locked for statistical analysis.

### Confidentiality {27}

All study-related information will be stored securely at the study site. All participant information will be stored in locked file cabinets in areas with limited access. All reports, data collection, process, and administrative forms will be identified by a coded ID (identification) number only to maintain participant confidentiality. All records that contain names or other personal identifiers, such as locator forms and informed consent forms, will be stored separately from study records identified by code number.

### Plans for collection, laboratory evaluation, and storage of biological specimens for genetic or molecular analysis in this trial/future use {33}

Not applicable, no specimens will be collected.

## Statistical methods

### Statistical methods for primary and secondary outcome {20a}

#### Primary outcome

The comparison between the two treatment groups of the mean dyspnea during the first 24 h will be performed by a Mann Whitney test taking a one-sided alpha risk of 10% to limit the risk of missing a difference. The primary outcome will be analyzed in the modified intent to treat population considering all patients randomized having received at least one dose of intervention in the group in which they will be randomized.

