### Methods for additional analyses {20b}

There is no plan to conduct any additional analyses.

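### The primary Mann-Whitney test is valid and correctly sized, but it leaves the baseline Dyspnea-VAS unused; prespecified adjustment would give a modest gain and protect against chance imbalance

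*Protocol article*

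**What the plan says.** In the protocol article, Statistical methods {20a}, Primary outcome, the comparison of the 24-h mean Dyspnea-VAS "will be performed by a Mann Whitney test taking a one-sided alpha risk of 10% to limit the risk of missing a difference". No covariate is named.

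A baseline value exists for every patient. Eligibility criteria {10} require a Dyspnea-VAS of at least 40 mm, and the data recorded at inclusion cover "Physiological values: temperature, blood pressure, respiratory rate, VAS-dyspnea, VAS-anxiety". Sequence generation {16a} describes 1:1 allocation in permuted blocks and mentions no stratification.

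Methods for additional analyses {20b} says: "There is no plan to conduct any additional analyses".

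Sample size {14} assumes that "the reduction of mean Dyspnea-VAS over the first 24 h (primary outcome) would be 25 mm", "with a standard deviation of 26 mm", at 80% power and one-sided 10% alpha, and arrives at 22 patients (11 per group) for a non-parametric test.

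**The concern.** The dyspnea score at entry is a natural candidate predictor of the mean dyspnea score over the next 24 hours. The plan relaxes alpha to 10% one-sided so as not to miss an effect, yet leaves out a measurement already in hand that could serve the same aim without raising the false-positive rate.

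With 11 patients per arm the groups can also differ at baseline by chance. An unadjusted comparison carries part of that difference into the estimated effect. The result is meant as a signal for deciding on a larger trial, so a distortion in either direction matters. Because the article names the primary test and states that nothing further is planned, this is a stated choice and not a detail left to an unseen analysis plan.

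**Working it through.** **1. The planned sample size reproduces.** Inputs from Sample size {14}: difference 25 mm, SD 26 mm, one-sided alpha 0.10, power 0.80.

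n per arm = 2 × (1.2816 + 0.8416)² × 26² / 25² = 9.75. Dividing by 0.955, the efficiency of the Mann-Whitney test under normality, gives 10.21, so 11 per arm and 22 in total. Simulated Mann-Whitney power at 11 per arm (40,000 trials, normal data) is 0.80, with type I error 0.095-0.098.

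**2. How large the correlation can be.** The documents give neither the baseline SD nor the correlation. Assume a baseline SD of 12-18 mm. Correlation = slope × baseline SD / outcome SD. If 1 mm more at baseline means at most 1 mm more in the 24-h mean (slope ≤ 1), the ceiling is 12/26 = 0.46 to 18/26 = 0.69. At a slope of 0.5 (also an assumption) the correlation is 0.23-0.35.

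**3. Power with adjustment.** 11 per arm, 25 mm, SD 26 mm, one-sided 10%, simulated:

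| Correlation | Mann-Whitney | Rank ANCOVA | Linear ANCOVA |
|---|---|---|---|
| 0 | 80% | 79% | 81% |
| 0.2 | 80% | 79-80% | 82% |
| 0.3 | 80% | 81% | 83-84% |
| 0.5 | 80% | 86% | 89% |

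Type I error of both adjusted tests stays at about 10%. In a separate simulation at a slope of 0.5, Quade's test against Mann-Whitney gave 79.7% v 79.4% (baseline SD 12), 81.7% v 80.5% (SD 15) and 81.9% v 80.1% (SD 18).

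These are normal-data figures. A planned mean of 12 mm with SD 26 mm on a scale bounded at 0 cannot be normal, so the percentages are approximate.

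**4. Chance imbalance.** The standard error of the between-arm baseline difference is SD × √(2/11) = 0.426 × SD, so 5.1 mm (SD 12) to 7.7 mm (SD 18). The MCID implied by Sample size {14} is 25 / 2.5 = 10 mm. The chance of an imbalance above 10 mm in one given direction is P(Z > 10/5.1) = 2.5% to P(Z > 10/7.7) = 10%.

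**5. What an imbalance does to the unadjusted test.** An imbalance of 0.5 baseline SD shifts the unadjusted difference by correlation × 26 × 0.5. The chance of one above that size, counting both directions, is 24%. By normal approximation:

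| Correlation | Shift | Power: balanced → morphine arm worse | False-positive rate: balanced → morphine arm better |
|---|---|---|---|
| 0.3 | 3.9 mm | 0.85 → 0.74 | 0.09 → 0.165 |
| 0.5 | 6.5 mm | 0.87 → 0.67 | 0.07 → 0.21 |

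These are conditional on the imbalance. Averaged over randomizations, the test keeps its 10% level.

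**The case against.** The case for leaving the plan alone is substantial. Design and analysis agree: the trial is sized for a rank test and uses one, and the level holds. It is a pilot. Chance imbalance is already allowed for in the 10% error rate, so it adds variability and not systematic bias. All of that stands.

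The likely gain may also be small. Entry at 40 mm or more narrows the baseline range. Dosing follows the same rule in both arms, aimed at a score below 40 mm. The sponsor also expects that "our primary outcome would be 37 mm in the control arm", which is below the lowest baseline permitted, so scores are expected to fall on placebo too. Each of these may weaken the correlation, and at 0.2 or less rank ANCOVA gains nothing.

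Three stronger readings are tempting, and the documents do not support them:

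- A reader might infer that adjustment would lift power to 93% (rank) or 96% (linear), the simulated values at correlation 0.7. With an outcome SD of 26 mm and a baseline SD of 12-18 mm, that needs a slope above 1.
- A reader might infer that baseline imbalance could by itself produce a positive trial. The one-sided 10% threshold is about 1.28 × 26 × √(2/11) = 14 mm. A 10 mm imbalance shifts the outcome by 5 mm at slope 0.5 and by 10 mm at slope 1, short of the threshold either way. The chance of an imbalance above 10 mm in either direction is 5-19%, but only half of that favours morphine.
- A reader might infer that adjustment is free. The rank version loses about 1 point of power if the correlation is near zero.

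What survives is that the possible loss is about 1 point, while the possible gain is 6 points (rank) to 9 points (linear) at correlation 0.5, with protection against imbalance in addition.

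**Conclusion.** The point holds as a matter of efficiency and robustness, not as an error. The Mann-Whitney test is valid and the 22 patients match its stated power. The plan nevertheless leaves out a baseline value that it collects on everyone, and it plans no adjusted analysis, even as a sensitivity check.

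The gain runs from nothing, or a loss of about 1 point, at correlation 0-0.2 to about 6-9 points at 0.5, and becomes material only from about 0.4-0.5. This rests on an assumed correlation, an assumed baseline SD of 12-18 mm, a slope of at most 1 and normal data. That baseline is collected but unused is certain; the size of the benefit is not. A prespecified change is worthwhile because the cost is small and because an adjustment added after unblinding would carry little weight.

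**What to change.** Before database lock and unblinding:

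1. Prespecify one baseline-adjusted primary comparison of the 24-h mean Dyspnea-VAS, with the inclusion Dyspnea-VAS as covariate, at the same one-sided 10% level. Either rank ANCOVA (Quade), which stays closest to the planned rank approach, or linear ANCOVA would do; name one only.
2. Report the adjusted difference in mm from a linear ANCOVA with a two-sided 80% confidence interval, which matches the one-sided 10% level.
3. Keep the unadjusted Mann-Whitney test as a sensitivity analysis.
4. Amend Methods for additional analyses {20b} to match.

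The cost is protocol or analysis-plan wording and one degree of freedom: about 1 point of power for the rank version if the correlation is near zero. No extra patients or data are needed.
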